### 3 Trial Aims / Objectives / Hypotheses

For all research questions, the study population refers to adults with newly diagnosed with breast cancer who are undergoing treatment through the Breast Clinic at RPH.

Primary research questions:

- 1) Does the SMART program, compared with usual care, change health-related quality of life (primary outcome) measured 16-weeks and 12-months following randomisation?
- 2) Does the SMART program, compared with usual care, change peripheral muscle strength, muscle mass, exercise tolerance, exercise adherence and chemotherapy completion rates (secondary outcomes) measured 16 weeks following randomisation?

Secondary research questions:

- 1) Do factors such as adherence, treatment pathway and cancer stage moderate the magnitude of any change in primary or secondary outcomes? (i.e. moderator analysis)
- 2) What is the health care utilisation, absenteeism and presenteeism over the 12 months following randomisation? (descriptive analyses only, to guide patient expectations in regarding these outcomes)

- 3) Does performance on tests of peripheral muscle force-generating capacity and exercise tolerance, change with test repetition (i.e. is there a learning effect)? (can be answered by Honours students enrolled in the BSc physiotherapy at Curtin University)
- 4) What is the minimal detectable difference in health-related quality of life and exercise tolerance? (can be answered by Honours students enrolled in the BSc physiotherapy at Curtin University)
- 5) Do psychological determinants of behavioural change, such as capability, opportunity, and motivation affect adherence to the SMART program and physical activity maintenance?
- 6) Does the SMART program improve mood, and does mood influence adherence to the program and physical activity maintenance?

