## OTHER VARIABLES

**Descriptive variables** will be recorded such as age, sex, body mass index, employment status, co-morbid conditions, stage of cancer and details of cancer treatment.

**Healthcare utilisation and adherence with exercise** will be assessed in both groups. In the control group, this will be documented during the monthly phone calls and exercise diaries. In the experimental group, this will be monitored by asking each participant during the weekly supervised sessions and also using exercise diaries (see Section 4, Monitoring). Regarding healthcare utilisation, we will ask each participant to recall the number of; (i) visits to the Emergency Department, (ii) inpatient admission days, (ii) outpatient appointments and, (iii) visits to any other healthcare provider (Y/N, who, number of visits). Regarding adherence with exercise, we will ask each participant to recall the number of minutes spent engaging in moderate or vigorous intensity exercise and details regarding any resistance exercise.

**Absenteeism and presenteeism** will be assessed using the iMTA productivity cost questionnaire (Bouwman 2015).

**Global rating of change** will be assessed by asking participants, on completion of the SMART exercise program, to indicate if their health-related quality of life or exercise tolerance had 'improved', 'worsened' or 'stayed the same'. Those participants who rated their walking ability as 'improved' or 'worsened' will then be asked to rate the degree of change on a seven-point scale (1 a little better to 7 a great deal better).

**Feasibility and acceptability** will be measured using; (i) Quantitative data from an acceptability and feasibility questionnaire, and (ii) qualitative data from exit interviews. These are described below:

*Quantitative data* will be collected using a questionnaire asking participants to rate their perceptions of the SMART exercise program (e.g., "*I thought the SMART exercise program was easy to understand*"). Participants can rate each item on a five-point scale (1 "*I don't agree at all*" to 5 "*I totally agree*"). Four open-ended items at the end of this questionnaire allow participants to include additional feedback (e.g., "*What did you like about the SMART exercise program?*").

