- What is the health care utilisation, absenteeism and presenteeism over the 12 months following randomisation?

This is an exploratory question and data will be described using mean and standard deviation.

*The third secondary research question is:*

- Does performance on tests of peripheral muscle force-generating capacity and exercise tolerance, change with test repetition (i.e. is there a learning effect)?

This will be assessed using one-way repeated measures analysis of variance (ANOVA). That is, for each participant, data collected over consecutive trials (5 attempts for each measure of muscle force and 2 attempts for the 6MWT) compared to explore if there is an effect of test repetition on these outcomes.

*The fourth secondary research question is:*

What is the minimal detectable difference in health-related quality of life and exercise tolerance?

This will be assessed using anchor-based approach via a Receiver Operating Characteristic curve. This curve will determine the optimal operating point to discriminate between participants who rate themselves as changed vs unchanged at the end of the SMART program.

*The fifth secondary research question is:*

Do psychological determinants of behavioural change, such as capability, opportunity, and motivation affect adherence to the SMART program and physical activity maintenance?

This will be assessed using correlations and a Multiple Regression Analysis of the data from psychological determinant measures (COM-B factors, impairment in functioning, intention, self-efficacy, habit, and mood) across all time-points for each participant. Data from the exit interviews will also be analysed using qualitative methods (such as thematic analysis) to explore participants' reasons for engagement (or lack of engagement).

*The sixth secondary research question is:*

Does the SMART program improve mood, and does mood influence adherence to the program and physical activity maintenance?

This will be assessed using correlations between mood data from the PANAS (across all timepoints) and physical activity engagement.

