## **Sample Size**

Sample size calculation has been conducted using the EORTC QLQ BR-30 (continuous data) as the dependent variable. To detect a difference between the experimental and control groups in this outcome of 8 (which has been estimated as the minimal clinically important difference), assuming a standard deviation of 20.52 (based on previously published literature) (Karsten 2022), with an  $\alpha = 0.05$  and  $1-\beta = 0.8$ , we will need to 104 participants in the experimental group and 104 participants in the control group. In order to account for 20% drop-out, we plan to recruit a sample size of 130 participants in each group. This means we aim to recruit 260 participants over 24 months (recruitment rate of 11 per month).

We believe that this recruitment rate is realistic. This is because, we have recently completed an audit of the RPH Breast Clinic (GEKO number 50167). The Data, Digital and Innovation (DDI) group at RPH compiled information from WEBPAS and showed that 993 adults were treated with surgical breast procedures and/or chemotherapy treatment for BC at the RPH Breast Clinic between 01/07/2021 to 30/06/2023. This is equivalent to 41 people per month. This means that our recruitment fraction for this study will be 27%.

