**1) What are likely to be the most important findings?**

- The effect of the SMART program on a range of patient centred outcome measures.
- The minimal detectable difference for measures of health-related quality of life and exercise tolerance in this patient population.
- Information regarding optimisation of measures of muscle force and exercise tolerance.
- Descriptive data on absenteeism and presenteeism.
- The effects of individual differences in psychological determinants of behaviour change (COM-B factors, impairment in functioning, intention, self-efficacy, habit, and mood) on physical adherence and maintenance.

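### Secondary question 4 asks for a minimal detectable difference, but the planned anchor-based ROC analysis estimates a minimal perceived change, so the result would carry the wrong name

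*Protocol*

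**What the plan says.** Protocol section 3 poses the fourth secondary question: "What is the minimal detectable difference in health-related quality of life and exercise tolerance". Section 9, Statistics and Interim Analysis, repeats the question and gives one method for it: "This will be assessed using anchor-based approach via a Receiver Operating Characteristic curve". The operating point on that curve is chosen to "discriminate between participants who rate themselves as changed vs unchanged at the end of the SMART program".

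The matching anchor is the global rating of change in section 7, Other Variables. Participants are asked "to indicate if their health-related quality of life or exercise tolerance had 'improved', 'worsened' or 'stayed the same", and some then rate the degree of change on a seven-point scale.

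Section 15, under the question "What are likely to be the most important findings", lists this item: "The minimal detectable difference for measures of health-related quality of life and exercise tolerance in this patient population".

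The Sample Size part of section 9 uses a different term for its 8-point target, "which has been estimated as the minimal clinically important difference".

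**The concern.** A minimal detectable difference is a property of the measuring instrument. It is the smallest change unlikely to be noise alone, and it is derived from the standard error of measurement or from test-retest variability in people whose state is stable. An anchor-based ROC cut-point is a property of participants' judgements. It is the change score that best separates those who say they changed from those who say they did not. Neither quantity determines the other.

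The Protocol itself fixes both the named quantity and the method, so this is not detail left to a later analysis plan. A plan that followed section 9 faithfully would carry the mismatch forward. What is at stake is the meaning of one secondary result: a threshold of perceived change would be reported as the answer to a measurement-error question.

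**Working it through.** **1. Quantity against method.**
- Named quantity, in sections 3, 9 and 15: minimal detectable difference, for quality of life and for exercise tolerance.
- Planned method, in section 9: ROC curve, self-rated changed versus unchanged.
- Not planned for this question: a standard error of measurement, a reliability coefficient or limits of agreement.
- The third secondary question does compare repeated trials (five strength attempts, two six-minute walks), but by repeated-measures ANOVA aimed at a learning effect, and it does not include quality of life.

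**2. The plan's own figures.** The Protocol states no value for the minimal detectable difference. The only usable input is the SD of 20.52 from Sample Size. The calculation it belongs to reproduces: n per arm = 2 × (1.96 + 0.8416)² × 20.52² / 8² = 103.3, rounded up to 104, and 104 / 0.8 = 130 after 20% drop-out. Nothing in that calculation depends on this point.

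**3. Scale of a true detectable change (illustrative).** SEM = SD × √(1 − r), and MDC95 = 1.96 × √2 × SEM. The reliability r is assumed, because the Protocol gives none.
- r = 0.70: SEM = 11.24, MDC95 = 31.2
- r = 0.80: SEM = 9.18, MDC95 = 25.4
- r = 0.90: SEM = 6.49, MDC95 = 18.0
- r = 0.95: SEM = 4.59, MDC95 = 12.7

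**4. Does the ROC cut-point follow measurement error?** A small simulation used 104 participants, true change with mean 8 and SD 12, anchor noise with SD 3, the Youden cut-point and 100 repeats; all inputs except the SD of 20.52 and the 104 are assumptions. With a perceived threshold of 8, the mean cut-point was 9.0, 8.5, 7.8 and 7.7 at r = 0.70, 0.80, 0.90 and 0.95, while MDC95 fell from 31.2 to 12.7. With thresholds of 4 and 12 the cut-points were 5.1 to 6.8 and 9.9 to 11.4. The cut-point moved with the perceived threshold, pulled somewhat towards the assumed mean change. It did not move with MDC95.

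**5. Could the scheduled data supply a detectable difference?**
- *Six-minute walk.* Section 7 has two walks per assessment and records the longer. The two walks give within-session error of a single walk. With independent normal errors and no learning, the SD of the longer of two is √(1 − 1/π) = 0.826 of the single-walk SD, so single-walk error overstates that of the recorded score by 1 / 0.826 = 1.21, about 21%. Between-day variation is left out, which acts in the other direction. The figure is therefore neither a clean estimate nor a guaranteed lower bound.
- *Quality of life.* The questionnaires are scheduled at baseline, mid-way, end of intervention and 12 months. No repeat in a stable state is planned. Change over 16 weeks of cancer treatment in those who report no change mixes real fluctuation with error.

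**The case against.** The best defence is that only the label is wrong. Section 9 says openly what the curve separates, section 7 describes the anchor, and some authors use these terms loosely. That is largely right, and it limits the point to a correction of wording. It does not remove it: the Protocol has a separate term for an important difference in Sample Size, and the term it uses in the three other places has an established meaning that the method does not deliver.

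Three stronger readings are tempting, and the documents support none of them.
- *A main result of the trial is compromised.* This is the fourth secondary question, which section 3 says Honours students can answer. The section 15 list is preparatory work for a framework that will be adapted as the project goes on.
- *The published threshold would be too small by a known factor.* A reader might divide the MDC95 values by 8 and get, for example, 12.7 / 8 = 1.6 or 25.4 / 8 = 3.2. But 8 is the between-group planning difference, not an ROC result. The reliabilities are assumed, the SD belongs to one quality-of-life score, and nothing can be computed for the walk test.
- *Clinicians would be told that the value exceeds an individual's measurement noise.* No passage says so. The term invites that reading, but the claim is not made.

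It is also fair to object that minimal important change would be no better as an automatic replacement. A changed-versus-unchanged split does not measure importance, and as described it could put those who worsened together with those who improved. That objection stands and shapes the fix.

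**Conclusion.** The point holds as a mismatch between the named quantity and the method. Followed exactly, section 9 yields a minimal perceived change and reports it as a minimal detectable difference. The conclusion rests on the text and on standard measurement definitions, not on the assumed reliabilities. The range of about 13 to 31 points only shows that a measurement-error threshold could lie well away from a perceived-change threshold; it is not an estimate of the discrepancy in this trial. The primary endpoint, primary analysis and sample size are not affected. The correction is worth making because the result is intended for publication and the change is almost free.

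**What to change.** - In section 3, section 9 (fourth secondary question) and section 15 (expected findings), rename the quantity to match the method. Use minimal perceived change if the split stays changed versus unchanged.
- Use minimal important change only if the seven-point degree rating in section 7 defines what counts as important, with improvement and worsening analysed separately. That route also needs the rating reworded: the follow-up is now tied to walking ability, and its end labels describe improvement only.
- On either route, confirm that the anchor will be collected as intended. Section 7 words it for completion of the SMART program, which may cover the experimental group only, and the rating has no row in the timing table.
- Do not report the ROC value as exceeding measurement error.
- If a detectable difference for the six-minute walk is also wanted, estimate within-session error from the two walks, label it within-session only, and allow for the recorded score being the longer walk. For quality of life, do not claim one, since no stable-state retest is scheduled.

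The cost is wording in three places, and a small change to the rating form if the importance route is chosen. No new assessment visit is needed.

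### The fourth secondary question asks for a minimal detectable difference, but its ROC analysis estimates a minimal important change, and the contrast as worded groups improved with worsened participants

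*Protocol*

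**What the plan says.** Section 3 and Section 9 pose the fourth secondary question as "What is the minimal detectable difference in health-related quality of life and exercise tolerance". Section 9 gives the method: "This will be assessed using anchor-based approach via a Receiver Operating Characteristic curve". The curve is to find the "optimal operating point to discriminate between participants who rate themselves as changed vs unchanged at the end of the SMART program". It does not say whether change is signed or absolute, or whether there is one curve or one per direction.

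The anchor is the global rating of change in Section 7 (Other Variables). Participants are asked "to indicate if their health-related quality of life or exercise tolerance had 'improved', 'worsened' or 'stayed the same". Those who report a change in either direction, now described in terms of walking ability, "will then be asked to rate the degree of change on a seven-point scale (1 a little better to 7 a great deal better"). The timing-of-outcomes table in Section 7 has no row for this item, although the text places it at completion of the program.

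Section 15, under the question "What are likely to be the most important findings", lists "The minimal detectable difference for measures of health-related quality of life and exercise tolerance in this patient population" as one of five items.

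**The concern.** Two things do not fit.

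First, the quantity named is not the quantity estimated. A minimal detectable difference is the smallest change that exceeds measurement error, and it comes from the scatter of repeat scores in stable people. An anchor-based ROC cut-point is the score change that best separates people who say they changed from those who say they did not, which is a minimal important change. The protocol plans no standard error of measurement, ICC or stable-participant analysis for quality of life. In its sample-size paragraph it already treats importance as a separate idea, with an 8-point minimal clinically important difference.

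Second, a two-way changed/unchanged contrast drawn from a three-answer anchor puts improved and worsened participants on the same side of the curve. Their score changes have opposite signs, so a single threshold on signed change cannot separate both from the unchanged group.

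At stake is a published threshold that others could use to interpret individual change or to size trials. It would carry the wrong name and, if a material share of participants worsen, would be too large.

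**Working it through.** **The plan's own figures.** The protocol gives no number for this question. Its only related calculation is the sample size: 2 × (1.96 + 0.8416)² × 20.52² / 8² = 103.3, so 104 per arm, and 104 / 0.8 = 130. This reproduces and does not depend on the point made here.

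**Step 1: size of a detectable difference.** The SD of 20.52 is from the sample-size paragraph. The ICC is not in the protocol and is assumed over a range. With SEM = SD × √(1 − ICC) and detectable change = 1.96 × √2 × SEM:

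| Assumed ICC | SEM | Detectable change (95%) |
|---|---|---|
| 0.95 | 4.59 | 12.7 |
| 0.90 | 6.49 | 18.0 |
| 0.80 | 9.18 | 25.4 |
| 0.70 | 11.24 | 31.2 |

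All four exceed the protocol's 8-point important difference, so the two quantities are not interchangeable. The protocol gives no SD for the six-minute walk distance, so no range is offered for it.

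**Step 2: effect of combining directions.** All inputs here are assumptions. Score changes are normal with means +10 (improved), 0 (unchanged) and −10 (worsened), and SD 15 in each group. 40% are unchanged, and the improved/worsened shares are 50/10, 40/20, 30/30 and 25/35%. Let w be the worsened fraction of the changed group, so w = 10/60, 20/60, 30/60 and 35/60.

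AUC: Φ(10 / (15√2)) = 0.681 for improved versus unchanged and 0.319 for worsened versus unchanged. The combined AUC is (1 − w) × 0.681 + w × 0.319.

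Cut-point: the Youden-optimal threshold c is where the densities of the changed and unchanged groups are equal. Dividing through by the unchanged density gives (1 − w)e^(kc) + w e^(−kc) = e^(100/450) = 1.2488, with k = 10/225 = 0.0444. Setting u = e^(kc), this is (1 − w)u² − 1.2488u + w = 0, and c = ln(u)/k at the larger root.

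| Worsened, % of all | w | u | Cut-point | AUC |
|---|---|---|---|---|
| Improved vs unchanged only | 0 | 1.249 | 5.0 | 0.68 |
| 10 | 0.167 | 1.350 | 6.8 | 0.62 |
| 20 | 0.333 | 1.551 | 9.9 | 0.56 |
| 30 | 0.500 | 1.997 | 15.6 | 0.50 |
| 35 | 0.583 | 2.418 | 19.9 | 0.47 |

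**Step 3: sensitivity to the inputs.** A simulation with different assumptions (means +16, 0, −16; SD 8, 12 or 16; true improved-versus-unchanged cut-point 8) shows the same pattern. With 40% improved, 30% unchanged and 30% worsened, the combined signed cut-point is 10.3, 12.7 and 15.8 for the three SDs, with AUC 0.54 to 0.56. With 10% worsened it is 8.4 to 9.8. With none worsened it is about 8. Absolute change does not repair it: across the mixes that cut-point runs from about 10.5 to 18.

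**Step 4: one model, two quantities.** In the Step 2 model, unchanged participants have a change SD of 15. SEM is then 15/√2, and the detectable change is 1.96 × 15 = 29.4, against an improved-versus-unchanged ROC cut-point of 5. The mismatch in name therefore matters even if nobody worsens.

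**The case against.** The strongest reply is that combining the two directions is inferred. The protocol never says that improved and worsened participants enter one curve, and the final SAP, which it says will be published, could split them. That stands as a limit: it is the plain reading of the ROC wording beside the three-answer anchor, and not an explicit instruction. It does not rescue the label, which is stated outright.

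The size of the bias also rests on assumed means, SDs and shares. A reader might infer that the cut-point is bound to be badly wrong; the documents do not support that. With 10% worsened it moves only from 5 to 6.8. The background figure that 23% reduce their activity during treatment is not a share of self-rated worsening and cannot fill the gap.

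Other stronger readings also fail:

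- The degree scale, labelled only "1 a little better to 7 a great deal better", might seem to corrupt the cut-point. The ROC as described uses only changed versus unchanged, so the scale does not enter it. The labels are still unusable for someone who worsened, and the shift to walking ability leaves quality of life without a degree rating. The questionnaires are in an appendix that is not shown, so the full item wording could not be checked.
- Asking the anchor on completion of the program agrees with the analysis text. An anchor-based threshold needs no randomised comparison, so asking both arms is a preference. The missing table row is a clerical gap.
- The question might be taken as a headline result. It is the fourth secondary question, which Section 3 says Honours students can answer, and one of five likely findings in a knowledge-translation list.

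**Conclusion.** The point holds as a correction to a secondary analysis. The target is misnamed: the planned method yields a minimal important change, whereas a detectable difference would be about 13 to 31 points (SD 20.52, assumed ICC 0.95 to 0.70). As worded, the contrast also mixes opposite directions of change. Under the Step 2 assumptions this roughly doubles the threshold at 20% worsened and quadruples it at 35%, with discrimination falling to chance. The inflation is conditional on how many worsen and vanishes on signed change if none do; the naming error does not.

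A reader might extend this to the trial's main result. Nothing supports that: the primary comparison, its power, the sample size and the 8-point difference behind it do not use this analysis.

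**What to change.** 1. Rename the target as the minimal important change in Section 3 (secondary question 4), Section 9 (fourth secondary question) and the Section 15 list.
2. Replace the single contrast with separate ROC curves on signed change: improved versus unchanged and, if numbers allow, worsened versus unchanged. Do this for quality of life and for six-minute walk distance, each with its own anchor item.
3. Correct the degree scale in Section 7 so that it has labels for worsening and refers to the same construct as the anchor question it follows.
4. Add the global rating of change to the timing table at 16 weeks.
5. If a detectable difference is also wanted, compute 1.96 × √2 × SEM from the baseline-to-16-week scores of participants who rate themselves as the same, with SEM = SD of their change / √2. Do not take it from the two walk tests within one assessment. The protocol itself examines those for a learning effect, and they do not give the error of a 16-week change.

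The cost is wording, a corrected anchor with one item per outcome in the existing 16-week assessment, and one table row. No new visit is needed. The anchor items should be settled before 16-week data are collected, because a faulty or missed rating cannot be recovered at analysis.

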## 8 Assessment of Safety

### Risks and benefits

This is a low risk study. Exercise during cancer treatments has been widely studied, reported as a safe intervention for individuals with cancer and is recommended as part of usual clinical care (Cormie 2018). Participants may experience some post exertional malaise and/or delayed onset muscle soreness, but the research team, trained physiotherapists, will ask about these symptoms every week and modify the program as required and also liaise with the treating medical team. The main risk to the participants in this study is inconvenience relating to the time and travel expense associated with attending the study assessments.

We will be assessing quality of life surveys. It is possible that participants will report low or reducing quality of life and/or depressive symptoms. Should these be identified we will recommend and refer the participant to the psychology support services, through the usual referral pathways within the Breast Clinic.

Regarding benefits, those allocated to the experimental group will receive the SMART program. We hope that this program will optimise participation in structured exercise and produce sustained improvements in health-related quality of life. If this is the case, we will endeavour to implement a similar program as part of routine physiotherapy care at RPH in the future.

Participants will be offered vouchers in compensation for travel costs for the face to face appointments and the time taken to complete the study assessments. These vouchers will be valued at \$15 for travel cost compensation and \$20 for time compensation to complete the assessments.

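### The ROC analysis for secondary question 4 contrasts changed with unchanged participants, but its anchor has two opposite kinds of change; read literally, this pools them and biases the cut-off upward if anyone worsens

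*Protocol*

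**What the plan says.** Protocol section 9 (Statistics and Interim Analysis, fourth secondary research question) names the method: "This will be assessed using anchor-based approach via a Receiver Operating Characteristic curve". It then describes a single curve whose optimal operating point is to "discriminate between participants who rate themselves as changed vs unchanged at the end of the SMART program". It does not mention the direction of change, does not say whether the change score is signed or absolute, and plans no second curve.

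The anchor is in section 7 (Other variables, Global rating of change). Participants are asked "to indicate if their health-related quality of life or exercise tolerance had 'improved', 'worsened' or 'stayed the same". Both non-neutral answers then lead to the same follow-up question on the size of the change, which uses one scale: "rate the degree of change on a seven-point scale (1 a little better to 7 a great deal better". That scale is labelled in the better direction only. The follow-up also speaks of walking ability, whereas the opening question covers quality of life or exercise tolerance.

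Section 15 (Publication) includes the resulting threshold in its list of likely most important findings: "The minimal detectable difference for measures of health-related quality of life and exercise tolerance in this patient population".

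**The concern.** A cut-off on a change score separates two groups when one tends to lie above the other. Improved participants tend to lie above those who stayed the same, and worsened participants below. If both are put in one changed class, that class surrounds the unchanged class, and one threshold cannot separate them properly. The cut-off then depends on the ratio of worsened to improved participants, so it describes the case mix of this trial and not the instrument.

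Some worsening is foreseeable. Section 8 (Risks and benefits) says: "It is possible that participants will report low or reducing quality of life and/or depressive symptoms". Section 2 describes treatment side effects that reduce fitness and quality of life. The likely harm is a threshold that is too high, so that real improvements below it would later be read as no change.

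**Working it through.** **The plan's own figures.** The protocol gives no AUC, cut-off or sample size for the ROC analysis, so there is nothing of that kind to reproduce. The trial sample size does reproduce, taking alpha as two-sided: 2 × (1.960 + 0.842)² × 20.52² / 8² = 103.3, so 104 per arm, and 104 / 0.8 = 130. It has no bearing on this point.

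**Inputs.** All inputs to the illustration are assumptions.
- Mean change is +d in improved, -d in worsened and 0 in unchanged participants, with d = 8. The 8 is borrowed from the Sample Size section for scale only.
- The SD of change, s, is the same in all three groups. The protocol does not give it, so it is varied from 5 to 20.52; the upper end is the SD in the Sample Size section.
- The worsened share of the changed class, w, is varied from 0 to 50%.
- Scores are normal, higher is better, and the cut-off maximises sensitivity + specificity - 1 (Youden).

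**Signed score, both directions pooled.**

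AUC = (1 - w) Φ(d / (s√2)) + w Φ(-d / (s√2)).

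Setting the derivative of the Youden index to zero gives (1 - w) u² - E u + w = 0, with E = exp(d² / 2s²) and u = exp(c d / s²). Hence

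c = (s² / d) × ln{ [E + √(E² - 4w(1 - w))] / [2(1 - w)] }.

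With w = 0 this is c = d / 2 = 4.0, whatever the SD. In this model any w above 0 gives a larger c.

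Example with s = 10 and w = 0.25: E = exp(0.32) = 1.377; √(1.8965 - 0.75) = 1.071; u = 2.448 / 1.5 = 1.632; c = 12.5 × ln 1.632 = 6.1. AUC = 0.75 × 0.714 + 0.25 × 0.286 = 0.61.

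Cut-off (AUC):

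| SD of change | w = 0% | w = 10% | w = 25% | w = 50% |
|---|---|---|---|---|
| 5 | 4.0 (0.87) | 4.3 (0.80) | 4.9 (0.69) | 6.1 (0.50) |
| 10 | 4.0 (0.71) | 4.7 (0.67) | 6.1 (0.61) | 10.5 (0.50) |
| 15 | 4.0 (0.65) | 4.8 (0.62) | 6.9 (0.57) | 15.4 (0.50) |
| 20.52 | 4.0 (0.61) | 4.9 (0.59) | 7.3 (0.55) | 20.8 (0.50) |

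At w = 50% a Youden maximum still exists, but it is of little use: the index is 0.07 at SD 10, against 0.31 at w = 0.

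**Absolute score, both directions pooled.** With equal and opposite shifts the share w drops out, and the cut-off solves cosh(c d / s²) = E, so c = (s² / d) × arccosh(E).
- d = 8: the cut-off is 6.1 at SD 5 (AUC 0.78), 10.5 at SD 10 (0.59) and 20.8 at SD 20.52 (0.52).
- d = 12, where the directional cut-off is 12 / 2 = 6.0: 7.4 at SD 5, a ratio of 7.4 / 6.0 = 1.2; and 15.8 at SD 15, a ratio of 15.8 / 6.0 = 2.6.

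Nothing cancels here, but random fluctuation in either direction counts as change, and the cut-off rises with the noise.

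**Sampling spread.** In 2,000 simulated samples (104 participants, 40% unchanged, d = 8, SD 10, signed score), the median cut-off was 4.1, 4.5, 5.7 and 8.9 at w = 0, 10, 25 and 50%. The central 95% at w = 0 ran from -3.8 to 11.8.

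**The case against.** Pooling is inferred. The protocol does not say that improved and worsened participants are combined, and because direction is recorded, separate curves remain possible with the planned data. A final SAP is promised and could settle the matter. This stands as far as it goes. But the protocol does more than leave the contrast open: it states one curve, one operating point and two classes, and against a three-answer anchor the natural reading of the changed class is both directions.

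A reader might infer that gains and losses cancel and that the cut-off is wrong. The documents do not support that. Cancellation needs a signed score, and an AUC of 0.50 needs about equal numbers in each direction. No cut-off has been published or computed, and none is distorted on a signed score if nobody worsens. At a 10% worsened share the shift is under one point in the illustration, and at 104 participants the sampling spread of a Youden cut-off is wider than the bias at either 10% or 25%.

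The worsened share is also unknown. The background cites falling quality of life two years after diagnosis and reduced activity during treatment, but gives no self-rated worsening rate at 16 weeks. The anchor is asked on completion of the SMART program; if only that arm answers, the share could be small. The protocol does not settle this.

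A reader might also infer that an absolute score is always far off, by a factor of about 2.5. That size belongs to one assumed SD; with the same 12-point shift the factor is about 1.2 at SD 5.

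Finally, this is the fourth of six secondary questions, flagged as one that Honours students could answer. That limits its weight, although the same protocol lists the result among its most important findings.

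**Conclusion.** The point holds in a conditional form. Read literally, the ROC contrast in section 9 merges two opposite answers of the anchor in section 7. If any participants worsen, the signed-score cut-off is biased upward and discrimination falls: from 4.0 points to 4.3-4.9 when 10% of the changed class has worsened, to 4.9-7.3 at 25%, and to an AUC of 0.50 at 50%. An absolute score also raises the cut-off, by an amount that depends on an SD of change the protocol does not give. These sizes rest on assumed symmetric shifts, equal SDs and normal scores, and they show direction and rough scale only. Sampling error does not excuse the bias: it shrinks with more data, and the bias does not. The effect is confined to secondary question 4. The primary analysis and the sample size are unaffected.

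**What to change.** In section 9, fourth secondary research question, replace the changed-versus-unchanged contrast with two contrasts on the signed change score: improved versus stayed the same, and worsened versus stayed the same. Report a separate threshold for each. State in advance that deterioration will be reported descriptively if few participants worsen.

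In section 7, Global rating of change, give the seven-point scale labels for degree of worsening, and word the follow-up so that it matches the opening question on quality of life or exercise tolerance.

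The cost is a few sentences and one extra ROC run on answers already planned, with no added visits or participants. The labels need to be in place before the anchor is administered, and the contrasts before it is analysed. The drawback is that the deterioration threshold may be imprecise.
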